## Abstract

High-intensity functional concurrent training (HIFCT) has emerged as a form of training characterized by constantly varied functional movements adapted to individual fitness levels. Previous studies have reported positive effects on muscular strength, cardiorespiratory fitness, body composition, and psychological well-being; however, evidence regarding HIFCT interventions in school-aged children remains limited. Therefore, the aim of the present study protocol is to evaluate the effects of an 8-week HIFCT programme on muscular strength, cardiorespiratory fitness, body composition, anxiety, stress, and self-esteem in children aged 10–12 years. Physical fitness, anthropometric variables, and psychological outcomes will be assessed before and after the intervention using validated field-based tests and questionnaires. This study may provide novel evidence regarding the feasibility, safety, and potential effects of HIFCT programmes in the school setting. The study protocol was registered at ClinicalTrials.gov (NCT07552844) and approved by the Córdoba Research Ethics Committee (IMIBIC, Córdoba, Spain; protocol code SICEIA-2025-000408).

## 1. Introduction

Childhood and adolescence represent critical periods for physical, psychological, and social development, as well as for the establishment of lifestyle habits that may persist into adulthood [1]. In this context, regular participation in physical activity has been identified as one of the main protective factors against the development of cardiometabolic diseases, psychological disorders, and sedentary behaviors [2]. Nevertheless, a progressive decline in physical activity levels among children and adolescents has been observed over recent decades, with a substantial proportion of young people failing to meet current international health recommendations [3]. This situation has been associated with increasing rates of childhood obesity, deteriorations in physical fitness, and a greater prevalence of emotional problems such as anxiety, stress, and low self-esteem [4].

Current evidence indicates that structured exercise programmes provide significant benefits for both physical and mental health in children and adolescents [5]. In particular, muscular strength and cardiorespiratory fitness are strongly associated with metabolic, functional, and cardiovascular health outcomes [6]. Consequently, international organizations recommend the inclusion of strength and conditioning activities from an early age, provided that they are appropriately supervised and adapted to participants’ developmental characteristics [7,8,9].

Among the exercise modalities currently used to improve health-related fitness, high-intensity functional concurrent training (HIFCT) has emerged as a promising approach. Unlike traditional concurrent training models, which typically separate resistance and aerobic exercise into distinct sessions or training blocks, HIFCT integrates strength and cardiorespiratory stimuli within the same session through functional, multi-joint exercises performed at moderate-to-vigorous intensities [10,11]. This training approach incorporates varied and dynamic activities which may be particularly suitable during childhood by promoting engagement, enjoyment, and sustained participation in physical activity [12,13]. The increasing popularity of HIFCT in both recreational and sports settings has generated growing scientific interest in its potential effects on health and physical performance [14]. Previous studies have reported that HIFCT interventions may improve body composition, muscular strength, and cardiorespiratory fitness, leading to reductions in body fat percentage and increases in lean body mass among adults and physically active children and adolescents [13,14]. These adaptations are particularly relevant during childhood and adolescence, which are considered critical periods for the prevention of metabolic and cardiovascular diseases associated with sedentary behaviors and excess adiposity [5].

Beyond physical health outcomes, regular participation in physical exercise has also been associated with improvements in several psychological outcomes among children and adolescents. Recent systematic reviews indicate that physical activity may contribute to reductions in symptoms of anxiety, stress, and depression, while also improving self-esteem, emotional well-being, perceived physical competence, and health-related quality of life [15,16]. Furthermore, this has been proposed as an attractive exercise modality for children due to its capacity to enhance intrinsic motivation and enjoyment [17,18]. Additionally, the dynamic and cooperative nature of this type of training, together with the variety of tasks and the social component present during the sessions, may promote feelings of group belonging and personal satisfaction [19].

Importantly, the implementation of HIFCT in pediatric populations requires careful adaptation to participants’ developmental characteristics. The age range of 10–12 years is particularly relevant, as this period represents a key stage for the acquisition of fundamental movement skills, motor competence, and physical fitness, as well as for the establishment of long-term physical activity habits [20,21]. Within this developmental context, HIFCT may be a suitable training modality because it combines varied functional movement patterns with strength- and cardiorespiratory-oriented stimuli in a dynamic format that can be individually adapted to children’s abilities and interests. This rationale is consistent with current recommendations from the National Strength and Conditioning Association and the 2014 International Consensus, which support appropriately prescribed, progressive, and supervised youth neuromuscular training programmes in children and adolescents [20,21]. These recommendations are further aligned with pediatric guidance emphasizing technical competency, qualified supervision, and gradual progression in youth training. Importantly, no prospective study of supervised youth training programmes involving strength-oriented exercise has reported growth plate injuries, and supervised training appears to be associated with lower injury rates than many common youth sports [21]. Accordingly, the present intervention was designed as a non-competitive child-oriented HIFCT programme based on bodyweight exercises, light external loads, age-appropriate movement patterns, and individualized progression under professional supervision. Acknowledging the substantial developmental heterogeneity within this age range—particularly regarding motor competence, attention span, and physical capacity—the present protocol incorporates age-stratified training to ensure that programme content is appropriately matched to participants’ developmental stage [21].

Despite the growing popularity of HIFCT and its potential benefits for physical and psychological health, evidence in school-aged children remains limited. Most available studies have been conducted in adult or athletic populations [10], and relatively few randomized controlled trials have examined HIFCT programmes specifically designed for children and adolescents [6,8]. Moreover, substantial heterogeneity exists across studies regarding training structure, exercise selection, intervention duration, supervision procedures, and age-adaptation strategies, which limits the comparability of findings and the ability to draw clear conclusions regarding the feasibility, safety, and effectiveness of child-oriented HIFCT interventions [9]. Furthermore, relatively few studies have simultaneously examined physical fitness, body composition, and psychological outcomes within the same HIFCT intervention in pediatric populations [13,14,15].

The age range of 10–12 years was selected because it represents a developmentally appropriate stage for the implementation of a supervised HIFCT programme involving multi-joint movement patterns, progressive external loading, and competency-based exercise progressions [22]. In addition, recent pediatric resistance training research has specifically targeted schoolchildren aged 10–12 years when designing and evaluating structured resistance-based interventions, supporting the practical and methodological relevance of this age range for supervised strength-oriented programmes [22]. This rationale is further supported by the neuromuscular characteristics of late childhood, a developmental stage in which relevant improvements in force-producing capacity and neuromuscular function have been described [23]. Moreover, strength gains appear to be mediated predominantly by neural rather than hypertrophic mechanisms [20], with reported training-induced adaptations including enhanced motor unit recruitment, higher firing frequency, improved neural drive, and better intra- and intermuscular coordination [24].

Therefore, the aim of the present study protocol is to evaluate the effects of an 8-week HIFCT intervention on muscular strength, cardiorespiratory fitness, body composition, anxiety, stress, and self-esteem in children aged 10–12 years. It is hypothesized that children allocated to the HIFCT intervention will demonstrate greater improvements in muscular strength, cardiorespiratory fitness, body composition, anxiety, stress, and self-esteem than those assigned to the control group.

## 2. Materials and Methods

### 2.1. Study Design

The present study is designed as a randomized controlled trial aimed at evaluating the effects of an 8-week HIFCT programme in school-aged children between 10 and 12 years old. The study protocol follows the SPIRIT [25] (Standard Protocol Items: Recommendations for Interventional Trials) guidelines for clinical trial protocols, including the SPIRIT schedule (Figure S1) and the SPIRIT checklist (Supplementary Table S1). Participants will be randomly assigned to either an experimental group or a control group. Baseline and post-intervention assessments will be performed before (pre-test) and after (post-test) the intervention period. Moreover, the CONSORT (Consolidated Standards of Reporting Trials) statement has been considered in the study design report [26]. Participants allocated to the experimental group will complete a supervised HIFCT programme specifically designed for children aged 10–12 years, with session content, exercise complexity, and training demands adapted to the developmental characteristics and movement competency of this age group.

### 2.2. Study Setting

The study will be conducted in Córdoba (Spain). Participant recruitment and baseline assessments will be performed at a public primary school, while the intervention sessions and physical fitness assessments will be conducted at a specialized HIFCT facility located in Córdoba. The intervention programme will be supervised by professionals specialized in pediatric physical exercise and HIFCT. The center will provide the facilities, equipment, and technical staff required for the intervention at no cost to participants or their families.

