### 2.5. Blinding

Due to the nature of the exercise intervention, participants, families, and trainers cannot be blinded to group allocation. However, outcome assessors will be blinded to group allocation during baseline and post-intervention assessments. Participants and families will be instructed not to disclose their group allocation to the assessors during the post-intervention evaluations. Data analysis will be performed using coded group labels whenever feasible to reduce analytical bias.

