All intervention sessions and assessment procedures will be supervised by qualified professionals specialized in pediatric physical exercise and HIFCT in order to ensure participant safety and minimize the risk of injury during exercise practice. In addition, the study will follow quality assurance and Good Clinical Practice procedures throughout all phases of the research process. Before the start of the intervention, all professionals involved in programme delivery will be familiarized with the study protocol, session structure, exercise progressions, and safety procedures to ensure standardized implementation.

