### 2.9. Outcomes

All outcome variables will be assessed at baseline (pre-test) and immediately after the 8-week intervention period (post-test). The study will evaluate physical fitness, body composition, and psychological outcomes in children aged 10–12 years using validated field-based tests and questionnaires (Figure S2). All baseline and post-intervention assessments will be completed during a single evaluation session lasting approximately 60–90 min. To minimize fatigue, physical fitness tests will be administered in a standardized order with adequate recovery periods between assessments according to established testing protocols. Participants will receive standardized instructions and verbal encouragement throughout the testing session. Familiarization trials will be provided when required by the testing protocol to ensure adequate understanding of the procedures and to promote valid test performance. Before the strength assessments, all participants will perform a standardized warm-up protocol consisting of: (i) a general warm-up including light running, skipping, heel-to-glute movements, arm circles, wrist and ankle rotations, lunges, and changes in direction; (ii) a specific warm-up for jump including controlled squats, low-intensity jumps, and lunges with trunk rotation; (iii) a specific warm-up for handgrip dynamometry involving squeezing a rubber ball and wrist flexion-extension exercises; and (iv) a specific warm-up for the medicine ball throw including shoulder rotations, light medicine ball throws, and core activation exercises.

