##### Body Fat Percentage

Body fat percentage will be assessed using bioelectrical impedance analysis according to the International Society for the Advancement of Kinanthropometry (ISAK) guidelines. Participants will be assessed barefoot and wearing light clothing following standardized anthropometric procedures [44].

Psychological assessments will be administered on the same day as the physical evaluations at baseline and post-intervention. Participants will complete the questionnaires in a quiet and controlled environment under researcher supervision.

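### The venue of the baseline shuttle run is contradictory, and on either reading the fitness post-tests are held where only the HIFCT arm has trained

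*Protocol article*

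**What the plan says.** Section 2.2 assigns venues in one sentence of two halves: "baseline assessments will be performed at a public primary school, while the intervention sessions and physical fitness assessments will be conducted". The second half, read to its end, says "the intervention sessions and physical fitness assessments will be conducted at a specialized HIFCT facility located in Córdoba", with no restriction to post-test.

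Section 2.9 measures every outcome at both time points and adds: "All baseline and post-intervention assessments will be completed during a single evaluation session lasting approximately 60–90 min". The text under Body Fat Percentage adds: "Psychological assessments will be administered on the same day as the physical evaluations at baseline and post-intervention".

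On blinding, section 2.5 says that trainers cannot be blinded but that "outcome assessors will be blinded to group allocation during baseline and post-intervention assessments". Its one stated safeguard is to ask children and families not to reveal their group at post-test. Section 2.7 says: "All intervention sessions and assessment procedures will be supervised by qualified professionals specialized in pediatric physical exercise and HIFCT".

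The limitations in the Discussion treat the facility only as a question of realism and of how well results carry over to ordinary schools. They do not treat it as a possible source of measurement or detection bias.

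**The concern.** A baseline fitness test is both a baseline assessment (school) and a physical fitness assessment (facility). With a single session per time point, both statements cannot hold, so the reader cannot tell where the primary outcome is measured at baseline.

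The post-test venue is less uncertain, and that raises the second issue. Section 2.2 places fitness tests at the training site. By then one arm knows that site well and the other does not. The 20-m shuttle run ends on missed lines or when the child chooses to stop, and it is run with verbal encouragement, so comfort and confidence in the setting can affect the score. Such an effect arises after allocation, on one arm only. Randomization cannot balance it, and the analysis cannot separate it from the training effect.

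An assessor at that site may also see how at ease a child is there, or how a coach greets the child. Asking families to stay silent does not cover such cues.

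**Working it through.** **1. The venue statements side by side**

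| Source | Baseline fitness tests | Post-test fitness tests |
|---|---|---|
| 2.2, first half | School | Not addressed |
| 2.2, second half | Facility (no time restriction) | Facility |
| 2.9 | One session with all other baseline assessments | One session with all other post-test assessments |
| Body Fat Percentage | Same day as questionnaires | Same day as questionnaires |

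Two readings are possible:

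- Reading A: baseline fitness at the school, post-test fitness at the facility.
- Reading B: all fitness tests at the facility, so that the first half of 2.2 is wrong or covers only part of baseline.

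Both put post-test fitness at the facility.

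**2. Exposure to the site before post-test**

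Section 2.8.2 gives 8 weeks × 2 sessions = 16 sessions for HIFCT (S1 to S16 in Table 2) and none for controls. Under reading B each arm has also been there once, for baseline testing before randomization (section 2.4).

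**3. What cancels and what does not**

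Let g be growth and retest change, v the effect of a venue change, f the extra effect of knowing the site, and τ the training effect.

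- Mean change in HIFCT = g + v + f + τ
- Mean change in control = g + v
- Difference = τ + f

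Under reading A, v may be non-zero but drops out. Under reading B, v = 0. In both, f stays in the contrast. Under B, f is the effect of 16 sessions on top of one earlier visit, so it may be smaller.

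**4. The plan's own figure**

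Inputs from section 2.10: changes of 1.7 and 0.2, SDs of 1.9 and 1.6, two-sided α 0.05, power 0.80, allocation 1:1.

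- Difference = 1.7 − 0.2 = 1.5 mL/kg/min
- Pooled SD = √((1.9² + 1.6²)/2) = √3.085 = 1.756, stated as 1.76
- d = 1.5/1.76 = 0.852 (the article states 0.86)
- Noncentral-t power with n = 23 per group: df = 44, noncentrality = d × √(n/2) = 0.852 × √11.5 = 2.89, power = 0.807; with d = 0.86, power = 0.814

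Both values of d give 23 per group, so the stated total of 46 reproduces.

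**5. How much an unequal familiarity effect would matter**

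The documents give no value for f. The values b below are assumptions. The calculation uses the same test with τ = 0, SD 1.76 and 23 per group, and noncentrality = (b/1.76) × √11.5.

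| Assumed b (mL/kg/min) | Share of the planned 1.5 | b/1.76 | Two-sided rejection rate |
|---|---|---|---|
| 0 | 0% | 0 | 5.0% |
| 0.10 | 7% | 0.057 | 5.4% |
| 0.25 | 17% | 0.142 | 7.6% |
| 0.50 | 33% | 0.284 | 15.6% |
| 0.75 | 50% | 0.426 | 29.3% |

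The row b = 0 also covers a venue change that acts equally on both arms.

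**The case against.** The strongest reply is that nothing here shows a bias. That is right, and several stronger inferences are not supported:

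- **That the primary outcome is biased.** A change of venue or surface reaches both randomized arms and cancels. Only a difference in familiarity could bias the contrast. The documents neither show nor size one, and zero is compatible with them. An estimate built from assumed shuttles gained and an assumed VO2max per stage would rest wholly on inputs the article does not give.
- **That coaches do the testing.** Section 2.5 lists trainers among those who cannot be blinded and then says assessors will be, which separates the two roles. Section 2.2 has the center supply staff for the intervention, not for assessments. Section 2.7 states a qualification and a safety purpose; it does not say that the same individuals do both. Section 2.8.1 trains researchers and exercise professionals together in test administration, but this does not make coaches assessors.
- **That HIFCT children are tested on equipment they trained with.** The shuttle run needs only two lines 20 m apart. The medicine ball is a real overlap, but for a secondary outcome.
- **That state anxiety at post-test is measured at the facility.** The article asks for a quiet, controlled setting and names no venue. The facility is an inference from the single-session and same-day rules.

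Section 2.9 also says that instructions are standardized. The SPIRIT schedule and Figure S2 are not shown and may state the venues.

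What remains is the conflict in the printed text, the unequal exposure to the post-test site, and a blinding safeguard limited to what families say. No section says that session staff must be absent from post-tests.

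**Conclusion.** The contradiction over where the baseline shuttle run takes place is a matter of text and needs no assumption. That fitness post-tests fall at a site where only the HIFCT arm has trained follows from section 2.2 on either reading.

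The consequence is a plausible risk, not a demonstrated bias. It rests on the assumption that knowing the site can change effort or pacing in a volitional test, and that assessors might pick up cues there. Its size is unknown. The table above shows only that, at 23 per group and with a planned difference of 1.5 mL/kg/min, an assumed advantage of 0.10 would hardly matter (5.4%), while 0.50 would roughly triple the false-positive rate (15.6%).

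The matter should be settled before the first baseline test, because analysis cannot separate such an effect from training afterwards.

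**What to change.** - **Section 2.2:** name one venue for all baseline and post-test assessments in both arms, preferably the school, which both arms know equally. If the facility must be used, give both arms the same familiarization visit before post-test.
- **Sections 2.5 and 2.7:** state that staff who deliver or supervise training sessions do not assess, encourage or attend at post-test.
- **Section 2.9:** check that the single-session wording agrees with the venue chosen.

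The cost is a few sentences, transport of portable test equipment and some school scheduling. The sample size does not change.

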### 2.3. Participants

Participants will consist of children enrolled at a public primary school. Recruitment procedures will ensure that none of the participants are engaged in structured extracurricular sports activities before the beginning of the intervention.

Participants will be randomly assigned to one of two study groups: (i) an experimental group, which will participate in an 8-week supervised HIFCT, or (ii) a control group, which will maintain their usual routines without participating in any structured physical exercise programme during the intervention period. To confirm compliance with these criteria, parents or legal guardians will complete a questionnaire regarding their child’s participation in organised physical activities outside school hours, including the weekly frequency and type of activity performed. Families of children assigned to the experimental group will also be instructed to avoid participation in additional structured sports activities during the intervention period.

To be eligible for participation, children must meet the following inclusion criteria: (i) be between 10 and 12 years old; (ii) be enrolled at a public primary school; (iii) not participate in extracurricular sports activities before the beginning of the intervention; (iv) be available to attend two weekly training sessions during the 8-week intervention period in the case of the experimental group; (v) present no medical, psychological, or behavioral contraindications that may limit participation in physical exercise; and (vi) provide written informed consent signed by parents or legal guardians.

Exclusion criteria will include: (i) musculoskeletal injuries, chronic diseases, or medical conditions limiting participation in physical exercise; (ii) formally diagnosed psychological, behavioral, or neurodevelopmental disorders that may interfere with safe participation in the intervention or with the completion of the outcome assessments, as reported by parents or legal guardians during the screening process; (iii) inability to attend the intervention sessions regularly; (iv) participation in structured extracurricular sports activities during the intervention period; and (v) absence of written informed consent from parents or legal guardians. Before participation, families will receive detailed written and verbal information regarding the study aims, procedures, benefits, and possible risks. Written informed consent signed by parents or legal guardians will be required before enrollment. Contact information will also be provided to resolve any questions related to the study procedures.

